#### Sample size calculation

The sample size was calculated with a conservatively estimated between-group effect size of 0.5 on the primary outcome measure WAS [31], based on an expected improvement in the experimental group from 6 (moderate work ability) to 8 (good work ability), an expected improvement in the control group from 6 to 7 (to take into account a potential ‘regression to the mean effect’) and a standard deviation of 2 [18, 46]. Based on previous studies [17, 21], this between-group effect size can be considered feasible. Based on two-sided testing, a significance level of 0.05, a power of 0.8, and this expected between-group effect size, 126 participants have to be recruited. Based on trials on comparable vocational interventions in IA [15, 17, 19], we took into account a drop-out rate of 10% (i.e., 126/90 * 100), which resulted in a sample size of 140 participants (70 in each arm). Considering a threefold higher prevalence of RA over axSpA in the Netherlands, we expect both groups to comprise more people with RA than axSpA.

#### Process evaluation

The process of the trial will be evaluated both quantitatively and qualitatively, comparable to previous and ongoing other trials from our group [63, 64]. For the quantitative evaluation, PTs will report process parameters after each treatment session (in OnlinePROMS®), including participant adherence, number of treatment sessions, the content of the applied treatment, and adverse events. Based on these parameters, PT treatment fidelity can be assessed. For the qualitative evaluation, a random sample of 10 participants and 10 PTs will be selected and invited for semi-structured interviews to discuss experiences, barriers and facilitators with regard to the intervention. The semi-structured interviews will be conducted after the selected participant has completed the 12-month assessment.

### Statistical analysis

#### Primary analysis

A multilevel, regression analysis – with levels of patient and time point – will be performed using linear mixed modeling. Primary outcome measure WAS will be analyzed as a dependent variable, using the study group (intervention vs control), stratification variables (i.e., disease (RA vs. axSpA), disease duration (< 5 vs. > 5 years), current sick leave at randomization (yes or no)) and other potential confounders as independent variables. All analyses will be performed according to the intention-to-treat principle. Statistical significance will be accepted at *p*-values of less than 0.05 (two-sided testing).

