### Study procedures

During the recruitment period, information about the study will be shared with all rheumatology departments and outpatient clinics in the Netherlands and through various public media. Potentially eligible participants interested in the study receive information about the study as much as necessary from a medical ethical perspective, with only minimal information about the content of the experimental intervention, namely that it is PT-delivered and includes exercise therapy and advices regarding work, and will be subsequently screened by the researcher (NB). If a potential participant meets the eligibility criteria and consents, the treating rheumatologist will be contacted to confirm the clinical diagnosis. Potential participants will be included after receiving a confirmation of the diagnosis and informed consent. Participants will formulate and rate one specific work-related limitation in physical functioning and two specific other limitations in physical limitations in daily life, using the Patient Specific Complaints Numeric Rating Scale (PSC NRS) [32] during a telephone conversation with the researcher (NB). Baseline data (T0) and follow-up assessments, administered at 3-months (T3), 6-months (T6) and 12-months (T12) after baseline, will be collected through online questionnaires.

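### The primary model does not say how baseline WAS enters, lists no time or group-by-time term, and leaves its further covariates open

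*Protocol article*

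**What the plan says.** The Primary analysis section of the protocol article specifies a two-level linear mixed model (patient, time point) with WAS as the dependent variable. The listed independent variables are study group, disease, disease duration, current sick leave at randomisation, "and other potential confounders as independent variables". Nothing further is said about which confounders are meant or how they will be chosen.

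Other sections bear on this:

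- Study procedures: "Baseline data (T0) and follow-up assessments" are collected by online questionnaire, and Study design places measurements at baseline, 3, 6 and 12 months, with 12 months as the primary endpoint.
- Randomization and blinding: the stratification factors are disease, disease duration and current sick leave. WAS is not one of them.
- Sample size calculation: the effect is framed as change from a starting score of 6, including "an expected improvement in the control group from 6 to 7".
- Secondary analysis: similar analyses are planned for T3, for T6, for the whole follow-up and for all secondary outcomes.

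**The concern.** The outcome's own baseline is the obvious covariate for a repeated score, and here it is collected at no extra cost. The section goes as far as naming covariates, yet it does not name this one and does not say whether T0 is a covariate or one of the repeated outcomes. It also lists no term that would isolate the 12-month difference from the other visits.

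The open phrase adds a second problem. Under randomisation there is no systematic confounding to remove, so potential confounders has no defined content. It allows covariates to be picked after baseline tables or outcomes have been seen, and the primary estimate then depends on that choice. Because the secondary analyses follow the same model, the ambiguity carries over to them.

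At stake are the precision of the primary estimate, what that estimate means (a 12-month effect or an average over visits), and whether the model is fixed in advance.

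**Working it through.** **Step 1. Reproduce the plan's own figure.** Inputs from Sample size calculation: "Based on two-sided testing, a significance level of 0.05, a power of 0.8"; "conservatively estimated between-group effect size of 0.5 on the primary outcome measure WAS", that is 8 versus 7, a difference of 1 point; and "a standard deviation of 2".

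n per arm = 2 × (1.960 + 0.842)² × 2² / 1² = 62.8, rounded up to 63, so 126 in total. This agrees with "126 participants have to be recruited". Allowing for 10% drop-out, 126 / 0.90 = 140. Both figures reproduce, with no credit taken for baseline adjustment. (A t-based calculation gives 64 per arm, 128 in total, which is close enough.)

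**Step 2. Three readings of the listed terms.**

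1. *T0 WAS is not used.* Precision is given up (Step 3), and a chance baseline difference stays in the realised estimate (Step 4).
2. *T0 WAS is one of the repeated outcomes.* With a group main effect and no group-by-time term, the pre-treatment visit, where the expected difference is zero, is averaged into the effect. For illustration, take a constant effect of 1 point at T3, T6 and T12 with complete, equally weighted visits. The group coefficient is then (0 + 1 + 1 + 1) / 4 = 0.75, or 75% of the true effect.
3. *T0 WAS is one of the other potential confounders.* Then its use is a decision still to be made.

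**Step 3. Precision if T0 WAS is unused.** The documents give no correlation ρ between T0 and T12 WAS, so 0.3 to 0.7 is an assumption. For a single-visit comparison at 63 per arm:

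- unadjusted SE = 2 × √(2/63) = 0.356
- adjusted SE = 0.356 × √(1 − ρ²)
- power = Φ(1/SE − 1.960)

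| ρ | SE | Fall in SE | Power |
|---|---|---|---|
| unadjusted | 0.356 | – | 80.1% |
| 0.3 | 0.340 | 5% | 83.7% |
| 0.5 | 0.309 | 13% | 90.0% |
| 0.7 | 0.254 | 29% | 97.6% |

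The noncentral t distribution gives 79.5% unadjusted, then 83%, 89.5% and 97%.

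**Step 4. Chance imbalance.** A one-SE baseline difference moves the unadjusted 12-month estimate by ρ × 0.356, which is 0.11, 0.18 or 0.25 points at ρ = 0.3, 0.5 or 0.7. A difference at the 95% limit (1.96 SE) moves it by 0.21, 0.35 or 0.49 points, against a planned effect of 1 point. With the 12-month SD held at 2, these shifts do not depend on the baseline SD, because the regression slope rescales with it.

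**The case against.** The strongest reply is that a journal article need not print the full model. The text does not exclude T0 WAS: the time-point level could carry it as a repeated outcome, and the open phrase could include it. The separate analyses planned for T3, T6 and total follow-up suggest that visit-specific contrasts are intended. An analysis plan that is not shown may settle all of this, and blinding of the analysts limits selective choice of covariates.

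Part of this stands. A reader might infer that the plan leaves baseline WAS out, but the text shows only that its role is undefined. The reply does not rescue the section, though. It does list covariates and closes the list with an open category, the terms needed for a 12-month contrast are not among them, and blinded analysts do not make a model pre-specified.

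The size of the gain is also open to challenge, fairly. The comparator in Step 3 is a single-visit two-group comparison, whereas the plan is a repeated-measures model that already adjusts for current sick leave, which is plausibly related to WAS. Entry at WAS of 7 or below (or through recent sick leave) may narrow the baseline range and lower ρ. At ρ = 0.3 the gain is modest.

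Three further inferences are tempting and not supported:

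- *The trial is underpowered.* It is not: 126 and 140 reproduce without adjustment.
- *The unadjusted estimate is biased.* Over randomisations it is unbiased. Chance imbalance affects the realised estimate and its precision.
- *The QALY analysis has the same defect.* Economic evaluation states no regression model and refers to national guidelines, so its silence on baseline utility is not a stated error.

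**Conclusion.** The point holds as one of specification. The primary model does not name baseline WAS or say how T0 enters, lists no time or group-by-time term, and admits unlisted covariates without a selection rule. Each reading of the listed terms has a cost: forgone precision, a diluted group effect, or an unspecified choice.

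If T0 WAS goes unused, the forgone gain is a 5% to 29% smaller standard error and about 4 to 17 points of power above the planned 80%. This rests on an assumed correlation of 0.3 to 0.7 and a single-visit comparison, so it is illustrative. If T0 is an outcome under a group main effect only, the estimate is about 75% of the true effect, given a constant effect and complete, equally weighted visits.

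Neither the validity of the randomised comparison nor the planned sample size is in question.

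**What to change.** Settle the role of T0 first, because the same value should not be both outcome and covariate. Either of these serves:

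- WAS at T3, T6 and T12 as outcomes, with T0 WAS as a continuous fixed covariate; or
- a constrained-baseline model with T0 in the outcome and a common baseline mean for both arms.

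In both, include time and group-by-time, keep the three stratification factors, and name the T12 contrast as the primary estimate. T3, T6 and the average over follow-up then come from the same model.

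Replace the open phrase with a list of covariates fixed before unblinding, or move it to a sensitivity analysis. Pre-specified prognostic covariates may stay in the primary model; only the open-ended choice has to go.

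Apply the same form to secondary outcomes measured at T0. Global perceived effect has no T0 value, so it needs none.

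The cost is wording only: the T0 values are already being collected, and the sample size does not change.

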#### Secondary analysis

Similar analyses will be performed for the secondary time points T3 and T6, as well as for the total follow-up period, and with all secondary outcome measures. Only Global Perceived Effect (GPE) will be analyzed as a dichotomous variable (‘completely recovered’ and ‘much recovered’ vs. all other responses) using logistic multilevel analysis. Furthermore, effect sizes from all clinical outcome measures will be calculated.

#### Economic evaluation

For the economic evaluation, a trial-based cost-utility analysis will be performed, relating costs to quality-adjusted life years (QALYs). Societal costs will include healthcare utilization, informal care and work-related costs, assessed using patient questionnaires at 3, 6 and 12 months. QALYs will be calculated using the Dutch tariff for the EQ-5D-5L [65], assessed at baseline, 3, 6, and 12 months. Analyses will be performed in accordance with the Dutch guidelines for economic evaluations [66], with extrapolation beyond the one-year trial period. The primary analysis will be from a societal perspective with friction cost method to value productivity, whereas secondary analyses follow the human-capital approach and a healthcare perspective [67]. Costs will be related to outcome using net-benefit analysis, with multiple imputation to account for missing data.

#### Data management

All the data of the participants will be pseudonymized with assignment of a study number to every participant. The key to the study numbers will be stored in a separate file on the server of the Leiden University Medical Center (LUMC). Only the research team, an auditor from the LUMC and national and international supervisory authorities can access the participants’ personal information. The collected data will be stored for 15 years on a local server at the LUMC and a backup of the data will be stored at the LUMC.

## Discussion

Work ability of people with RA or axSpA is considerably reduced compared to the general population [8]. Despite the observed need for vocational interventions, research on the (cost-)effectiveness of vocational interventions is limited. To our knowledge, this is the first study on the (cost-)effectiveness of a PT-led, vocational intervention in people with RA or axSpA. Based on existing evidence and clinical experience, we have integrated all potentially effective treatment modalities into a single intervention, delivered by PTs specifically trained for this purpose. We expect that the incorporation of these individually effective modalities, with an embedded focus on work, will lead to a moderate effect as well as substantial cost savings through reduced sick leave and improved work productivity. Therefore, we hypothesize that a multimodal, PT-led, vocational intervention in (self-)employed people with RA or axSpA and a reduced work ability is effective and cost-effective compared to usual care.

We would like to acknowledge two (potential) study limitations about the population. First, as we include two patient groups (i.e., RA and axSpA), our study sample could be considered relatively heterogenous. However, people with RA as well as axSpA experience comparable symptoms, including joint pain, stiffness, fatigue [1–3] and reduced health-related quality of life [3, 4]. Furthermore, we include a homogenous sample from a work perspective, namely people with reduced work ability but still at work or less than 6 months on sick leave, as this population is expected to profit most from our intervention. Therefore, we expect these two patient groups to respond similarly to our intervention. Second, since participants in this study cannot be blinded to their randomization, it cannot be ruled out that control participants will seek a similar (PT) intervention that may lead to contamination and thereby reduce the contrast between our two arms. However, we do not expect this to occur, as work is usually not addressed in current practice [68, 69]. Nevertheless, we will carefully record the use of any healthcare or other services during the 12-months of follow-up. This enables us to demonstrate the level of contamination.

Furthermore, we would like to mention three (potential) limitations regarding the design of the study. First, the number of sessions in our intervention (10 to 21 sessions during a 12-month follow-up period) appears to be relatively extensive compared to other vocational intervention studies in IA, in which the number of sessions was between one and 12 [15–21]. Due to the complexity of the concept of work ability, a multimodal approach with a long follow-up period is considered necessary to achieve sustainable changes in work ability. Second, although we tested a draft version of our intervention for feasibility in a small group of four patients, unexpected barriers in its execution may arise if applied on a larger scale which could impact the outcomes of the study. Third, for practical reasons, we only include people in whom the cost of the intervention is covered by their complementary health insurance (or if not, people are willing to pay it out-of-pocket). This may lead to a selection bias, although a majority of the people with IA (namely 76% [25]) in the Netherlands have this coverage. Because we carefully capture this eligibility criterium (inclusion criterium 6), we have insight into the extent of this barrier after the completion of the trial.

To conclude, as the study is still ongoing the results are not available yet, the scientific implications of this publication are limited. However, given the fact that limited research on the effectiveness of interventions to increase the work ability of people with RA or axSpA is available, for those interested in the evidence on this topic it is important to be aware of ongoing studies. The results of this study will provide insights in the (cost-)effectiveness of a multimodal, PT-led, vocational intervention in people with RA and axSpA and a reduced work ability.

## Data Availability

The data generated during this study will not be publicly available, but will be available upon reasonable request to the corresponding author.

## Abbreviations

IA: Inflammatory arthritis
RA: Rheumatoid Arthritis
axSpA: Axial SpondyloArthritis
RCT: Randomized Controlled Trial
PT: Physiotherapist
OT: Occupational Therapist
WAS: Work Ability Index – Single Item Scale
PSC NRS: Patient Specific Complaints Numeric Rating Scale
EQ-5D-5L: EuroQol
GPE: Global Perceived Effect
QALY: Quality-adjusted Life Year
ICTRP: International Clinical Trial Registry Platform
SAE: Serious Adverse Event
AE: Adverse Event
LUMC: Leiden University Medical Center
